### Recruitment

2.4

The clinical trial is currently recruiting participants. Patient recruitment started in October 2018. Estimated study completion date is May 1, 2019. The enrollment capacity was estimated to be 6 patients/mo.

### Participating centers

2.5

Eligible patients are selected from the visitors of the pediatric dental clinic of the Department of Pediatric Dentistry, Faculty of Dental Medicine—Medical University of Plovdiv, Bulgaria and treated in the laser dental office of the aforementioned.

### Assignment of interventions

2.6

#### Sequence generation

2.6.1

A computer-generated, permuted-block randomization sequence for allocation of first procedure is to be prepared. Patients are to be randomized to treatment allocation according to number of enrollment in the trial. In this split-mouth randomized controlled trial (RCT), every patient will receive both procedures. The patient will be randomized to receive at the first visit, placebo analgesic procedure and, at the second visit, laser pre-emptive analgesia or at the first visit—LA and at second one—placebo procedure.

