### Trial design

1.3

The trial to be conducted is a double-blind controlled clinical crossover experimental study with 2-way repeated measures design. Figure 1 summarizes the enrollment, intervention, and assessment schedule, all of which are in accordance with the Standard Protocol Items for Randomized Trials (SPIRIT) recommendations,^[9]^ shown in Table 1 . Patients and outcomes assessor are blinded for the study. Experimental group in this study consists of permanent upper jaw first molars, receiving pre-emptive LA prior to laser caries ablation, whereas control group consists of contralateral permanent upper jaw first molars with similar defects of the same patient, receiving placebo-analgesia prior to laser treatment.

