#### Inclusion criteria

2.2.1

1.Participants in the study are children 10 to 12 years old, compliant with the cognitive development of the child and the requirement for full root development for diagnostics with electrical pulp testing.2.Children, identified as positive or definitely positive through Frankl behavioral rating scale.3.Children who are not considered medically compromised or medically complex patients. The absence of disease is confirmed by anamnestic interview with a parent or a care-giver of the child and excludes general acute or chronic disease, cognitive impairment.4.Patients, requiring conservative treatment of occlusal or foramen caecum caries on 2 first permanent upper jaw molars without prior restorations or dental sealants. Lesions are to be classified as moderate caries by the International caries detection and assessment system (ICDAS) with code 03 or 04, which do not present spontaneous unprovoked pain, percussion or palpation pain or other symptoms, indicating of pulpal or periodontal pathology. Included are carious lesions only on vital teeth, involving up to half of the dentine thickness.5.Obtained informed consent from parents or gave-givers to participate in the study, in which procedures are explained in appropriate manner (see supplementary data file S1—“Informed consent” and supplementary data file S2—“Information leaflet”).

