#### Participant timeline

2.3.3

Each eligible patient undergoes 2 single-visit treatments of the 2 carious first upper jaw molars, receiving LA when undergoing treatment of 1 tooth and PA at the other visit during treatment of the homologous contralateral tooth. The 2 manipulations are performed by 1 operator, performing treatment of caries and restorative procedure. Outcomes are registered by the primary investigator in a clinical file (see supplementary data file S3 - “Clinical file”). A 7 to 21 day interval is allowed between one procedure and the other. The protocol to be used in the first procedure is randomly selected using a computer-generated list linked to sequence of enrollment in the trial.

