#### Allocation concealment mechanism and implementation

2.6.2

Randomization is based on treatment allocation sequence number. First procedure (PA—1; LA—2) is linked to number of enrollment in the study in Microsoft Excel table. Allocation sequence will be generated before start of the patient enrollment by the statistician. The operator will obtain each randomization allocation via a sequentially-numbered opaque sealed envelope prior to treatment, enabling the sequence to be concealed until the intervention is assigned. The outcomes assessor will not be aware of chosen treatment. Patients will be enrolled by the primary investigator.

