#### Blinding

2.6.3

The current study is designed as a double-blind trial. Patients as well as outcomes assessor are blinded for the study. The operator will get acquainted with procedure to be performed prior to treatment session. The clinicians involved in this study as operator and outcomes assessor are selected to be the only ones performing the manipulations in order to prevent bias.

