## Statistical methods

3

The unit of analysis will be the tooth for the split-mouth RCT (2 first permanent molars belonging to the same dental arch treated per patient). The data will be recorded and analyzed using SPSS 20.0. All data will be analyzed using an intention-to-treat analysis.^[14]^ Descriptive statistics will be calculated. Discrete variables will be summarized by frequencies or proportions. Continuous variables will be reported as means and standard errors or medians and range (depending on the distribution of the variables). Data will be checked for baseline differences between the treatment arms. If baseline differences do occur for any of the variables, they will be added to subsequent models to compensate for those differences using an analysis of covariance approach.

We will compare pain mean scores according to the visual analogue scale (VAS), containing numerical symbols. We will report the mean differences between groups and the associated 95% CIs. For the split-mouth RCT, with each patient being his or her own control, our statistical analysis will take into account the paired nature of data and the results will be analyzed by Student *t* test for paired samples.

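### Only the order of procedures is randomised, while the comparison is between teeth; nothing stated fixes which molar is treated first before the unblinded operator learns the allocation

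*Protocol article*

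**What the plan says.** The randomised element is described three times, each time as order alone:

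- Sequence generation (2.6.1): "A computer-generated, permuted-block randomization sequence for allocation of first procedure is to be prepared".
- Participant timeline (2.3.3): "The protocol to be used in the first procedure is randomly selected using a computer-generated list linked to sequence of enrollment in the trial".
- Allocation concealment (2.6.2): "First procedure (PA—1; LA—2) is linked to number of enrollment in the study in Microsoft Excel table". The code has two values and carries no tooth or side.

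The comparison is between teeth. Trial design (1.3) defines the control group as "contralateral permanent upper jaw first molars with similar defects of the same patient", and Statistical methods (3) states "The unit of analysis will be the tooth for the split-mouth RCT". The second visit takes the other upper first molar.

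On who knows the allocation and when, 2.6.2 says "The operator will obtain each randomization allocation via a sequentially-numbered opaque sealed envelope prior to treatment" and Blinding (2.6.3) says "The operator will get acquainted with procedure to be performed prior to treatment session". The Discussion (5) adds that the single operator cannot be blinded.

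On the lesions, Inclusion criteria (2.2.1) require "occlusal or foramen caecum caries on 2 first permanent upper jaw molars", with ICDAS code 03 or 04 and depth up to half the dentine. The Discussion names the need for symmetrical, similar conditions as a reason why many children are not eligible.

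**The concern.** In a split-mouth trial the treatment belongs to the tooth. Once the visit-1 procedure is known, choosing the visit-1 molar decides which molar gets LA and which gets PA. Randomising the order balances visit effects, such as familiarity with the procedure. It balances tooth effects only if the tooth is fixed independently of the allocation, and no section says that it is.

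The criteria narrow the difference between a child's two lesions but leave room for one: a code 03 lesion may be paired with a code 04, an occlusal lesion with one at the foramen caecum, and a shallower lesion with a deeper one. It is reasonable to expect depth and site to affect pain during ablation, which is the primary outcome. If the milder molar went to LA more often than chance, the imbalance would enter the paired VAS difference directly and look like an analgesic effect. Blinding the child and the assessor would not prevent this, because the selection would come before any outcome is measured.

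**Working it through.** **The plan's own figure.** Sample size calculation (2.3.4) gives 37 pairs and 10% drop-out, hence 41 recruits. 37 / 0.90 = 41.1 and 37 × 1.10 = 40.7; both agree with 41 to the nearest whole number. The 37 itself cannot be checked, because the effect size is not in the available text. Working back with a noncentral t, 37 pairs give 95% power at two-sided 5% for a standardised paired difference of about 0.61. That serves as a yardstick below.

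**Is the tooth protected by the stated scheme?**
1. Content of the list: PA first or LA first (2.3.3, 2.6.1, 2.6.2). No side.
2. Rule for the visit-1 molar: none in any section.
3. Operator's knowledge: allocation known before treatment (2.6.2), or before the session (2.6.3).
4. First study act tied to a tooth: baseline electric pulp test within the visit, 5 minutes before LA or PA (Clinical protocol, 2.2.4).
5. Consequence: the visit-1 tooth determines the treatment of both teeth.

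Points 1, 3 and 5 are stated or follow directly. That the tooth is still open when the envelope is opened is not stated; nor is the opposite.

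**What would selection do?** Let
- q = share of children whose milder molar gets LA (0.50 with no selection),
- δ = mean extra VAS pain of the worse molar, in SDs of the within-child difference.

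Bias in the paired difference = (2q − 1) × δ. With no true LA effect, the rejection rate of a two-sided 5% paired t test is the probability that a noncentral t with 36 degrees of freedom and noncentrality bias × √37 exceeds 2.028 in absolute value.

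| q | δ | Bias = (2q − 1)δ | Noncentrality | False-positive rate |
|---|---|---|---|---|
| 0.50 | any | 0 | 0 | 5.0% |
| 0.55 | 0.2 | 0.10 × 0.2 = 0.02 | 0.12 | 5.2% |
| 0.60 | 0.3 | 0.20 × 0.3 = 0.06 | 0.36 | 6.5% |
| 0.65 | 0.2 | 0.30 × 0.2 = 0.06 | 0.36 | 6.5% |
| 0.65 | 0.5 | 0.30 × 0.5 = 0.15 | 0.91 | 14.4% |
| 0.70 | 0.75 | 0.40 × 0.75 = 0.30 | 1.82 | 42.7% |

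Every q and δ is an assumption. The last row is extreme: its tooth gap of 0.75 SD is larger than the 0.61 SD effect that 37 pairs detect with 95% power. The 0.65 / 0.5 row has a bias of about a quarter of that effect (0.15 / 0.61 = 0.25).

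**The case against.** The strongest reply is that the decisive step is inferred. A reader might conclude that the operator opens the envelope and then picks the tooth. The document does not say so: it names nobody as choosing the molar and does not say that the choice is open at that moment. The tooth could be settled at enrolment, which is done by the primary investigator and not by the operator. A method-blind investigator tests the tooth before LA or PA is applied, so steering would mean directing that person to a particular molar. The article is condensed, and a convention may sit in the clinical file or the schedule figure, neither of which is shown. All of this stands as a reason not to claim that selection occurs. It does not supply a rule that fixes the tooth independently of the allocation.

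A reader might also infer that the two lesions need not be alike. That goes too far: Trial design and the Discussion treat similarity as an aim and as something that limits eligibility. What remains is that the listed criteria do not say how similar the lesions must be.

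Statistical methods already plans covariance adjustment for baseline differences. This helps with differences that are recorded per tooth, but not with features that influence a choice and are not recorded.

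Finally, mild assumptions move the error rate only to about 5% to 7%. That is correct, and the table includes them.

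**Conclusion.** The point holds in conditional form. The stated scheme randomises order and compares teeth, and it contains nothing that fixes the visit-1 molar before an unblinded operator knows the allocation. It therefore does not exclude the milder molar going to LA more often than chance. It would be wrong to read this as evidence that teeth are steered, or that the operator selects them; the text supports neither.

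Under assumed values the false-positive rate at 37 pairs lies between about 5% and 14% for small to moderate selection, and reaches 43% only in an extreme case. These figures rest on no true LA effect, a two-sided 5% test (the article does not state sidedness), and assumed q and δ. Since the route to bias is inferred from silence and the remedy is nearly free, this should be fixed; it is not a proven flaw in the data.

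**What to change.** For all children not yet randomised, do one of the following:

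- have the statistician's list assign the side treated at visit 1 as well as the order, both in the same sealed envelope; or
- have someone without access to the allocation record the visit-1 molar on the clinical file before the envelope is opened. This should not be the operator, who knows past allocations and, with permuted blocks, might anticipate some later ones.

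In either case, record ICDAS code and lesion site for each tooth before opening, so that the covariance adjustment already planned in Statistical methods can use them. If a rule for the visit-1 tooth already exists, state in one sentence what it is, who applies it and when.

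The cost is one column in the list, or one line on the clinical file, plus two recorded items per tooth that are already assessed for eligibility. The sample size stays at 37 pairs and 41 recruits. Trial status (5.1) reports 10 children enrolled by November 2018, so at that date 41 − 10 = 31 of the planned recruits could still be covered. For those already treated, report how the visit-1 tooth was chosen.

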#### Allocation concealment mechanism and implementation

2.6.2

Randomization is based on treatment allocation sequence number. First procedure (PA—1; LA—2) is linked to number of enrollment in the study in Microsoft Excel table. Allocation sequence will be generated before start of the patient enrollment by the statistician. The operator will obtain each randomization allocation via a sequentially-numbered opaque sealed envelope prior to treatment, enabling the sequence to be concealed until the intervention is assigned. The outcomes assessor will not be aware of chosen treatment. Patients will be enrolled by the primary investigator.

#### Blinding

2.6.3

The current study is designed as a double-blind trial. Patients as well as outcomes assessor are blinded for the study. The operator will get acquainted with procedure to be performed prior to treatment session. The clinicians involved in this study as operator and outcomes assessor are selected to be the only ones performing the manipulations in order to prevent bias.

#### Data collection, confidentiality, storage, and monitoring of study documents

2.6.4

According to the regulations of the Personal Data Protection Act, the collected paper forms will be stored in a secure manner in the Department of Pediatric Dentistry, Faculty of Dental Medicine, Medical University - Plovdiv, Bulgaria. Outcomes will be transferred electronically by the primary investigator after transmission of paper forms. Clinical research files will be stored in a locked, secure office. Data will be electronically stored on a double password-protected computer. Only the primary investigator and the statistician will have access to the final data set. The trial will be monitored by the research monitoring officer of Medical University—Plovdiv, verifying that the study is conducted in accordance with the Good Clinical Practice guidelines.

## Statistical methods

3

The unit of analysis will be the tooth for the split-mouth RCT (2 first permanent molars belonging to the same dental arch treated per patient). The data will be recorded and analyzed using SPSS 20.0. All data will be analyzed using an intention-to-treat analysis.^[14]^ Descriptive statistics will be calculated. Discrete variables will be summarized by frequencies or proportions. Continuous variables will be reported as means and standard errors or medians and range (depending on the distribution of the variables). Data will be checked for baseline differences between the treatment arms. If baseline differences do occur for any of the variables, they will be added to subsequent models to compensate for those differences using an analysis of covariance approach.

We will compare pain mean scores according to the visual analogue scale (VAS), containing numerical symbols. We will report the mean differences between groups and the associated 95% CIs. For the split-mouth RCT, with each patient being his or her own control, our statistical analysis will take into account the paired nature of data and the results will be analyzed by Student *t* test for paired samples.

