#### Primary outcome measures

2.3.1

Primary outcome measure to be assessed in this study is pain felt during the treatment, reported by the patient on a visual analogue scale (VAS) at the end of the treatment session.

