#### Sample size calculation

2.3.4

Given the lack of comparable research and the unknown population standard deviation we conducted a pretest with 20 subjects and considered the behavior of this subgroup as population estimate. To estimate sample size for the primary outcome—pain felt during laser ablation of moderate carious lesion, according to the VAS scale—we applied a *t* test for paired groups (G∗ Power software version 3.1),^[13]^ since we have 2 groups (first upper molar in right and left quadrant) on the same patient.

The effect size was determined using the formula 

Where SD is the pooled standard deviation—an average of the standard deviations of the experimental and control groups. The error was set at 5% and the power test at 95%. According to the calculation, a sample of 37 patients will be necessary to detect differences in pain. Since drop-outs are unavoidable when collecting follow-up data, this number needs to be adjusted for the estimated drop-out rate. During the pre-test, we had a drop-out rate of 5% for collecting the follow-up data and if we anticipated a higher drop-out rate for this study, we conservatively allowed for a 10% drop-out rate. Adjusting the sample size for this drop-out rate results in a sample of 41 patients needing to be recruited.

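### The primary paired t test leaves out the randomised visit order; adding a period term is a cheap improvement whose value depends on an unknown period effect

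*Protocol article*

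**What the plan says.** The Trial design section describes a "double-blind controlled clinical crossover experimental study with 2-way repeated measures design". Under Sequence generation, what is randomised is the order of the two procedures: "The patient will be randomized to receive at the first visit, placebo analgesic procedure and, at the second visit, laser pre-emptive analgesia", or the reverse. The method is stated as a "permuted-block randomization sequence for allocation of first procedure is to be prepared". Under Participant timeline, the visits are separated in time: "A 7 to 21 day interval is allowed between one procedure and the other".

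The primary outcome gives one value per visit: "pain felt during the treatment, reported by the patient on a visual analogue scale (VAS) at the end of the treatment session".

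Statistical methods fixes the comparison: "our statistical analysis will take into account the paired nature of data and the results will be analyzed by Student"'s t test for paired samples. No period or sequence term is named. The same section allows covariates by analysis of covariance, but only where baseline differences between the treatment arms are observed. Visit number is not a baseline variable of that kind. The section also states: "All data will be analyzed using an intention-to-treat analysis". Under Sample size calculation, 37 children are required and "we conservatively allowed for a 10% drop-out rate", which gives 41 to recruit.

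**The concern.** Each child's LA-PA contrast is also a contrast between a first and a second visit. By the second visit the child has already been through the whole laser procedure once, so reported pain may shift for reasons unrelated to LA, such as familiarity, fear, or knowing what the laser feels like. The shift has opposite signs in the two orders.

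A paired t test pools the differences from both orders as if they had one mean. If the orders are equally represented, the shift cancels from the estimate but inflates its standard error. If they are unequal, part of it stays in the estimate. At stake are the width of the confidence interval and, after uneven loss of children, the accuracy of the treatment effect itself.

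A paired test also needs both visits, so a child who attends only one contributes nothing unless a further rule is applied.

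**Working it through.** **Inputs from the protocol article.** 37 evaluable children, 5% error, 95% power and a paired t test (Sample size calculation); 10% drop-out and 41 recruited (same section); two randomised orders in permuted blocks (Sequence generation).

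**Assumptions.** Two-sided test and 1:1 allocation, neither of which is stated. The standardised effect has no readable value, so it is back-solved. The period effect is not given and is varied from 0 to 0.75.

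**Step 1: the plan's own figures.** For a paired t test, power = P(|T| > t₀.₉₇₅,₃₆), with noncentrality dz·√n. Setting n = 37 and power = 95% gives dz = 0.609 (noncentrality 0.609 × √37 = 3.71, critical value 2.03). A one-sided test would give 0.551. The 37 is thus consistent with dz of about 0.61 but cannot be verified independently. For drop-out, 37 × 1.1 = 40.7, rounded to 41, while 37/0.9 = 41.1. The 41 is reproduced to within one child, and 41 × 0.9 = 36.9 leaves about 37 completers.

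**Step 2: model.** Let D be the VAS under PA minus the VAS under LA, with SD 1 within each order and true mean τ. Let π be the visit-2-minus-visit-1 effect in the same units.
- LA first: mean of D = τ + π
- PA first: mean of D = τ − π

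The paired t test uses the overall mean of D, so its bias is π × (n_LA-first − n_PA-first)/37. Near balance, the SD it sees is about √(1 + π²): 1.03, 1.12 and 1.25 at π = 0.25, 0.5 and 0.75.

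The period-adjusted estimate is the average of the two order means, with standard error ½·√(1/n₁ + 1/n₂) and 35 degrees of freedom. It is free of π. Its noncentrality is 0.609/0.1645 = 3.70 at 18/19 (power 95.0%) and 0.609/0.1659 = 3.67 at 16/21 (power 94.6%).

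**Step 3: results for the paired t test** (simulation, 200,000 runs per cell). The two power figures are for the bias running against and with the treatment effect.

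| Completers by order | π (SD) | Size of bias (SD) | Power, paired t | Power, period in model | Type I error, paired t |
|---|---|---|---|---|---|
| 18/19 | 0 | 0 | 95% | 95% | 5.0% |
| 18/19 | 0.25 | 0.007 | 93.8% or 94.7% | 95% | 4.4% |
| 18/19 | 0.5 | 0.014 | 90.6% or 93.0% | 95% | 3.0% |
| 18/19 | 0.75 | 0.020 | 84.4% or 89.4% | 95% | 1.6% |
| 16/21 | 0.5 | 5/37 × 0.5 = 0.068 | 84.1% or 96.4% | 94.6% | 4.3% |
| 16/21 | 0.75 | 5/37 × 0.75 = 0.101 | 70.8% or 95.8% | 94.6% | 3.4% |

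**Step 4: how likely is 16/21?** Suppose 41 children start 20/21 and four are lost independently of order. All four come from the order of 20 with probability C(20,4)/C(41,4) = 4,845/101,270 = 4.8%. A split of 18/19 or 19/18 has probability (190 × 210 + 20 × 1,330)/101,270 = 65.7%.

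**Step 5: children with one visit.** Take four such children, two per treatment, added to 37 pairs in a mixed model. They are worth 0.5 to 2 extra pairs as the within-child correlation falls from 0.75 to 0. Power becomes 95.3% to 95.9% instead of 95.0%.

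**The case against.** The strongest reply is that nothing in the documents shows a period effect. First-time dental patients are excluded and only children rated positive or definitely positive on the Frankl scale enter, which should dampen novelty and fear. Permuted blocks start the orders close to balance, and 16/21 is unusual if losses are unrelated to order. Near balance the paired t test is conservative, not anti-conservative. All of this stands. It means the cost may be nil and must be shown as a range with both directions. It does not supply a reason to leave period out: laser treatment may still be new to these children, and adjustment costs almost nothing when it proves unnecessary.

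Three stronger readings are tempting, and the documents do not support them.
- A reader might infer that the plan simply wastes power. That holds only if a period effect exists, and at 16/21 the bias can raise power as well as lower it.
- A reader might infer that the intention-to-treat promise is broken. Children who stop for an injection still give a VAS score, so only missed visits are at issue. The rule for those may stand in a full protocol or SAP that is not shown, and the inflation to 41 already allows for the loss.
- A reader might infer that the electric and cold tests, measured at several times, will also be analysed by this t test. The t-test paragraph opens with VAS pain scores and does not mention those outcomes. Their model may properly be left to the SAP.

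**Conclusion.** The narrow point holds. The article fixes a primary analysis that omits the randomised order. With no period effect this costs nothing. At 18/19 completers it costs about 0 to 1 power point at 0.25 SD, 2 to 4 at 0.5 SD and 6 to 11 at 0.75 SD, and the test is conservative. At 16/21, an unfavourable split, the treatment estimate is off by about 0.07 SD (period effect 0.5 SD) or 0.10 SD (0.75 SD). The error can favour either procedure, and power is then 84% or 96%, and 71% or 96%, against about 95% with adjustment.

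These figures rest on dz = 0.609, a two-sided 5% test, 37 completers and assumed period effects. This is a cheap improvement, not a flaw that invalidates the trial.

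**What to change.** Make the primary analysis a linear mixed model of VAS with treatment and period (visit) as fixed effects and child as random effect, using every treated visit. Report the treatment difference with its 95% CI. Keep the paired t test as a sensitivity analysis. With complete pairs only, this model reduces to the period-adjusted comparison computed above.

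Including one-visit children also fits the stated intention-to-treat principle better than complete pairs, though the gain is under 1 power point.

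The cost is a change of wording before the data are analysed. Order and visit follow from the allocation list, so no extra children or measurements are needed. One degree of freedom is spent (35 instead of 36), with negligible power loss if there is no period effect.
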